#### Primary Outcome measures

1) The primary outcome measure in this study is sick leave duration until full RTW, defined as: duration of sick leave in calendar days from the day of surgery until full RTW in own or other work with equal earnings, for at least four weeks without (partial or full) recurrence [39]. This means that recurrences of sickness absence within four weeks after first day of full RTW, will be considered as belonging to the preceding period of sick leave, on condition that this is due to the consequences of the surgery. RTW will be measured by a monthly calendar of sickness absence.

#### Secondary Outcome measures

2) The total duration of sick leave (due to the consequences of the surgery) during the 26 weeks follow-up period; measured by a monthly calendar of sickness absence.

3) First RTW; measured by a monthly calendar of sickness absence.

4) Recovery; measured by a validated Recovery Specific Quality Of Life questionnaire RS-QOL(RI10) [40], an extended list of (graded) activities based on the detailed convalescence recommendations given to the patients of the intervention group [18] and a recovery monitor which is a tool of the e-health intervention of the intervention group.

5) Functional and general health status (Quality of life); assessed according to the standard Dutch version of the EuroQol [41] and the Short-form health survey (SF-36) [42,43].

6) Pain intensity; measured using Von Korff questionnaire [44].

7) Empowerment; assessed by the Dutch adaptation of the General Self-Efficacy Scale [45].

8) Health care usage; measured by the Tic-P questionnaire [46] and valued according to the prices in the guidelines for economic evaluation in the Netherlands [47].

9) The occurrence of complications in the post-operative period; assessed by questions based on the complication registration form of The Dutch Society of Obstetrics and Gynaecology (NVOG) [48]. Patients in the intervention group do also answer these questions more frequently through a tool of the e-health intervention, in order to register possible side effects of the intervention and to determine and inform them when symptoms require additional consultation of care providers or adaptation of convalescence recommendations.

#### Prognostic factors

10) Socio-demographic data; measured by the standard Dutch version of the EuroQol [41] and specific additional socio-demographic questions.

11) Type of surgery.

12) Complications during surgery; assessed by questions based on the complication registration form of The Dutch Society of Obstetrics and Gynaecology (NVOG) [48].

13) Work-related factors; measured by the Dutch Musculoskeletal Questionnaire (DMQ) [49], the Job Content Questionnaire (JCQ) [50] and specific additional work-related questions.

14) Pain perception and fear avoidance belief; assessed by the Tampa scale [51].

15) Sick leave duration in the past 3 months.

16) Expectations, intention and motivation of the employee about return to work after surgery [52].

#### Outcomes regarding process evaluation

A process evaluation will be performed only in the intervention group according to the Linnan and Steckler model [53]. These patients, their gynaecologists and employers will receive specific questions regarding the multidisciplinary care program, including the e-health intervention. These questions will measure:

17) Patient's attitudes, opinions and compliance regarding the convalescence recommendations and the tools of the e-health program.

18) Physicians' and employers' attitude en opinion regarding the multidisciplinary care program.

19) Satisfaction with care program and care providers; measured with the short version of the Patient Satisfaction with Occupational Health Services Questionnaire (PSOHQ) [54] and specific additional questions related to health care and care providers.

20) The use of the e-health intervention during the follow-up period (e.g. total login time, amount of mouse-clicks, use of particular tools, et cetera).

21) Suggestions for improvement of the e-health intervention.

22) Provided convalescence recommendations by the care providers according to the patients.

### Sample size

Power calculation was performed on the primary outcome (all kind of surgeries together). To achieve a power (1-β) of 80%, with a significance level (α) of 5% and considering a HR of 1.5 in favour of the intervention group, approximately 191 patients will be needed. Anticipating a 10% drop out rate, in total a sample size of at least 212 patients will be aimed for. To recruit this number of patients, the study will anticipate on a ten-month inclusion period.

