### Outcome Measures

#### Data-collection

The follow-up period will be 26 weeks after surgery (baseline). All the outcome variables are measured using self-report online questionnaires [35] and will be taken at baseline, 2, 6, 12 and 26 weeks after surgery. In general, the longer the recall period, the less accurate individuals are in reporting for example the use of health care services. Although no evidence on the optimal period is provided by literature, 12 and 26 weeks are frequently used and generally accepted [36]. Little agreement exists on the accuracy and validity of self-reported health care utilization and absenteeism data [37]. However, regarding sickness absence general consistency in the self-reporting can be relied on when recall is required within one month [37,38]. Therefore, in this study a monthly self-reported calendar of sickness absence per post was chosen to measure RTW. Furthermore, gynaecologists will complete questionnaires one day after surgery of each patient and at the end of the study. Employers will be asked to evaluate the e-health intervention eight weeks after the surgery of their employee. When patients, gynaecologists and employers do not fill out the questionnaires within one week, they will receive a reminder per email. If no response follows, they will be reminded by a telephone conversation. In addition to the questionnaires and calendars, the e-health intervention used by the intervention group will measure the use of the intervention, complications and (satisfaction with) recovery. Table 3 presents an overview of the outcomes and variables measured in this study.

**Table 3 T3:** Overview of outcome measures & variables in this study

Outcome measures & variables	T_0_ Baseline^d^	T_1_ 2 wks after surgery	T_2_ 6 wks after surgery	T_3_ 12 wks after surgery	T_4_ 26 wks after surgery
Primary					

1) Return to work^a^		measured monthly^e^			

Secondary					

2) Total duration of sick leave^a^		measured monthly^e^			

3) First RTW^a^		measured monthly^e^			

4) Recovery					

• Recovery specific QoL (RI-10)	X	X	X	X	X

• Performed activities			X		

• Performed activities measured by e-health intervention^b, c^		at least 2, 4, 7, 14, 21, 28, 42, 56, 84 days after surgery			

5) Functional and general health status (SF36, EuroQoL)	X			X	X

6) Pain intensity (Von Korff)			X	X	X

7) Empowerment (GSES)		X	X	X	

8) Health care usage (TicP)				X	X

9) Occurrence of complications during the post-operative period			X	X	X

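### The sample size section labels 191 as patients, but 191 is the number of sustainable return-to-work events needed; 212 women give 80% power only if about 90% of all randomised women have a confirmed event

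*Protocol article*

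**What the plan says.** The Sample size section powers the trial on the primary outcome, with all types of surgery combined, at 80% power and a 5% significance level. It states "considering a HR of 1.5 in favour of the intervention group, approximately 191 patients will be needed", and then "Anticipating a 10% drop out rate, in total a sample size of at least 212 patients will be aimed for". It mentions no number of events, no expected proportion returning to work and no allowance for censoring.

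Three other sections bear on this:

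- **Primary Outcome measures.** The outcome is time from surgery to full return, in own work or other work at equal earnings, held "for at least four weeks without (partial or full) recurrence". A relapse inside those four weeks is added to the earlier spell of sick leave only if it is a consequence of the surgery.
- **Data-collection.** Follow-up ends 26 weeks after surgery.
- **Data analysis.** The primary comparison uses Kaplan-Meier curves with a log-rank test, and a Cox model for the hazard ratio.

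**The concern.** The power of a log-rank or Cox comparison depends on the number of events. A patient who reaches week 26 without the event adds follow-up time but does not count towards the required total. If an event count is used as a patient count, the calculation assumes that everyone counted has the event.

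The protocol's own design leaves room for women who do not. The event must be sustained for four weeks and follow-up stops at week 26, so a full return that starts after about week 22 (26 − 4) cannot be confirmed within follow-up. Step 2 of the care program is for women not fully back at ten weeks. In Table 2 its last consultation, at weeks 22-23, still allows for a change in the planned return date.

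At stake is how the result is read. A non-significant result would be judged against a nominal 80% power that 212 women provide only under a high, unstated event proportion.

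**Working it through.** **Inputs.** From the Sample size section: hazard ratio 1.5, power 80%, significance level 5%, drop-out 10%, total 212. From the Randomization section: blocks of four and roughly equal groups, taken as 1:1. From the Data analysis section: log-rank test and Cox model. The protocol states neither the sidedness of the test nor the formula.

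**Step 1: reproduce 191.** Schoenfeld's formula with 1:1 allocation and a two-sided 5% level is

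events = 4 × (1.960 + 0.8416)² / (ln 1.5)² = 4 × 7.849 / 0.1644 = 190.97, rounded up to 191.

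This matches the stated figure exactly. The alternatives do not: one-sided Schoenfeld gives 150.4 (151 events) and two-sided Freedman gives 196.2 (197 events). Two-sided Schoenfeld is therefore inferred from the match. The formula contains no event probability, so 191 events equal 191 patients only if that probability is 1.

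**Step 2: reproduce 212.** 191 / 0.9 = 212.2. Drop-out accounts for the whole step from 191 to 212, so no event-proportion allowance is hidden in it.

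**Step 3: what 80% power requires of 212 women.** 191 / 212 = 0.90, so about 90% of all randomised women must have a confirmed event. Under the planned 10% drop-out there are 212 × 0.9 = 190.8 completers and 21.2 drop-outs.

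- Drop-outs contribute no events: the required share of completers is 191 / 190.8, in effect all of them.
- Drop-outs contribute at half the completers' rate: events = (190.8 + 21.2/2) × p = 201.4p, so p = 191 / 201.4 = 0.95.
- No drop-out at all: 212 × 0.90 = 190.8 events, power 80.0%.

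**Step 4: size of the shortfall.** The protocol gives no event proportion, so p, the share of completers with a confirmed event, is an assumed range. For d events:

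- power = Φ(√(d/4) × ln 1.5 − 1.960)
- hazard ratio detectable with 80% power = exp(2 × 2.8016 / √d)

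For example, with p = 90% and no events from drop-outs, d = 190.8 × 0.90 = 171.7. Power = Φ(6.552 × 0.4055 − 1.960) = Φ(0.697) = 0.757. Detectable hazard ratio = exp(5.603 / 13.10) = 1.53.

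| p among completers | Events, drop-outs add none | Power | Detectable HR | Events, drop-outs at half rate | Power |
|---|---|---|---|---|---|
| 100% | 190.8 | 80% | 1.50 | 201.4 | 82% |
| 95% | 181.3 | 78% | 1.52 | 191.3 | 80% |
| 90% | 171.7 | 76% | 1.53 | 181.3 | 78% |
| 85% | 162.2 | 73% | 1.55 | 171.2 | 76% |
| 80% | 152.6 | 71% | 1.57 | 161.1 | 73% |

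**The case against.** The strongest reply is that the loss may be small. Women lost to follow-up after a sustained return have already contributed their event, so the 10% margin can absorb some non-return. The eligibility criteria also favour return: the women are employed, have benign disorders, and are excluded for major health problems affecting recovery or for long prior sick leave. Step 2 and the weeks 22-23 consultation show that late non-return is foreseen, not that it is common. All of this stands, and it limits the size of the effect. It does not turn an event count into a patient count.

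A second reply is that a journal article condenses, and that the formula, sidedness and assumed event proportion may be in a fuller protocol. That would excuse leaving the event proportion out. It does not explain a figure that equals the event formula, is labelled as patients, and reaches the total through drop-out alone.

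A third is that the sidedness and formula are inferred. They are, but the match is exact, and Freedman's formula would not help: it needs 197 events, and 191 events would then give 78.9% power even with no censoring.

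A reader might go further and infer three things that the protocol does not support:

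- **That 80% power always requires every completer to return.** This holds only at 10% drop-out with no events from drop-outs.
- **That the trial is seriously underpowered.** No event proportion is given, and at 95% of completers the loss is about 2 points.
- **That any relapse within four weeks cancels the return.** The primary outcome definition counts a relapse only if it results from the surgery.

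**Conclusion.** The point holds as a wrong label with a consequence for the stated power. The figure of 191 is the required number of sustainable return-to-work events, and 212 women deliver 80% power only if about 90% of all randomised women have a confirmed event within 26 weeks. On the assumed range of 95 to 80% of completers returning, with drop-outs contributing none, power falls to between 78% and 71% and the detectable hazard ratio rises to between 1.52 and 1.57. If drop-outs contribute at half the completers' rate, the same range gives 80% to 73%.

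The event count and the inflation step follow from the protocol's own figures, given 1:1 allocation and a two-sided Schoenfeld calculation. The size of the shortfall rests on assumption. The primary test, its error rate and the effect estimate with its confidence interval are unaffected.

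**What to change.** In the Sample size section:

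1. State that 191 events, meaning confirmed full sustainable returns to work, are required, and name the two-sided test and formula if that is what was used.
2. State the proportion of women assumed to have a confirmed event by 26 weeks, and what is assumed about events among drop-outs.
3. Restate, for 212 women under those assumptions, either the power at a hazard ratio of 1.5 or the hazard ratio detectable with 80% power.
4. When describing the event there, keep the condition from the primary outcome definition that a recurrence within four weeks counts only if it is due to the consequences of the surgery.

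The sample size need not change. The cost is a few sentences and, unless about 90% of randomised women have a confirmed event, a stated power some points below 80%.

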### Blinding

Patients will be blinded for the allocated treatment. Treatment allocation (randomization) will take place by computer-generated block randomization after completion of baseline questionnaire and IC. After randomization, all patients will receive access to the e-health intervention. However, after logging into the website with their personal login credentials, the kind of information provided by the e-health intervention will depend on the group the patient is randomized for.

During recruitment, the patients will be told that in case they do not RTW within 10 weeks after surgery, they might be approached for supplementary care depending on the care program they are randomized for. Nevertheless, explanation will only be given about the comparison of two different types of information supply and peri-operative guidance and not about the content of peri-operative guidance according to the 'intervention' or 'control' group.

Due to the different treatments in both groups, therapists and researchers cannot be blinded for the allocated treatment of the patient.

### Data analysis

All statistical analyses will be performed at patient level, according the Intention-To-Treat (IIT) principle. To assess whether protocol deviations have caused bias, the results of the ITT analyses will be compared to per protocol analyses in which the patients who were not treated according to the intervention protocol, will be excluded. To examine the success of the randomization, baseline characteristics of the patients in both groups will be compared using descriptive statistics. If necessary, analyses will be adjusted for prognostic dissimilarities.

A Kaplan Meier analysis (including the log rank test) will be used to describe the association between the group allocation and the duration of sick leave until the first period of full sustainable RTW. The Cox proportional hazard model will be used to estimate hazard ratios for RTW and the corresponding 95% confidence interval.

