**Figure 1 F1:**
[figure not shown]
**Design of the RCT**.

The seven participating hospitals in this study will be six general (teaching) hospitals and one University hospital, all localized in or nearby Amsterdam: 1)The Amstelland Hospital; 2)The Flevo Hospital; 3) The Kennemer Gasthuis; 4) The Onze Lieve Vrouwe Gasthuis; 5) The Sint Lucas Andreas Hospital; 6) The Spaarne Hospital and 7) The VU University Medical Center.

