### Randomization

To prevent unequal randomization between hospitals, patients will be pre-stratified by hospital and type of surgery (laparoscopic adnexal surgery, total laparoscopic-/laparoscopic assisted-, vaginal- and abdominal hysterectomy). A computer-generated block randomization will be performed on individual level. The blocks consist of four characters to ensure roughly equal group sizes with each stratum and are randomly varying in sequence. Randomization will be executed by an (independent) research assistant, after the patient has completed baseline measurements and IC.

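### Randomisation is stratified by hospital and type of surgery, but adjustment is left to observed baseline imbalance; this makes the model data-dependent and may cost power, though the test stays valid

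*Protocol article*

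**What the plan says.** The Randomization section states that "patients will be pre-stratified by hospital and type of surgery (laparoscopic adnexal surgery, total laparoscopic-/laparoscopic assisted-, vaginal- and abdominal hysterectomy"; that is four surgery categories as listed. It adds: "The blocks consist of four characters to ensure roughly equal group sizes with each stratum". On sites: "The seven participating hospitals in this study will be six general (teaching) hospitals and one University hospital".

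The Data analysis section compares baseline characteristics between the groups descriptively and then states: "If necessary, analyses will be adjusted for prognostic dissimilarities". It names no covariate and no criterion. For the primary outcome, time on sick leave, it says: "A Kaplan Meier analysis (including the log rank test) will be used to describe the association between the group allocation and the duration of sick" (the quotation stops mid-phrase). For the effect estimate it says: "The Cox proportional hazard model will be used to estimate hazard ratios for RTW and the corresponding 95% confidence interval". Neither sentence mentions hospital or type of surgery.

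The Prognostic factors section has seven headings (items 10 to 16). Type of surgery is one of them; hospital is not. Table 3 shows six of the seven at baseline. The seventh, complications during surgery, is collected at 6 weeks.

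**The concern.** The design treats hospital and type of surgery as important enough to stratify on, yet the only stated route by which a covariate can enter the analysis is an imbalance seen afterwards. Two things follow.

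- **The rule works against the design.** Blocking within strata makes these factors look similar in the two groups, so a dissimilarity rule is unlikely to select them, however strongly they predict return to work. The case for adjusting for a prognostic factor rests on how well it predicts outcome, not on whether it happens to be imbalanced.
- **The primary model is not fixed.** Six baseline headings, several with more than one instrument, allow at least 2^6 = 64 covariate sets even if each heading counted as one variable. The choice would be made after seeing the data.

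At stake is some power, an effect estimate whose meaning depends on what was adjusted for, and a primary result open to the question of how its covariates were chosen.

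**Working it through.** **1. The plan's own figure.** The Sample size section gives HR 1.5, 80% power, 5% significance and about 191 patients. Two-sided Schoenfeld: 4 × (1.960 + 0.842)² / (ln 1.5)² = 190.97, so 191 is reproduced. With 10% dropout, 191 / 0.9 = 212.2, against the stated 212. The formula has no stratum term.

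**2. How far blocking balances the strata.** There are 7 hospitals × 4 surgery types = 28 cells, and 212 / 28 = 7.6 women per cell. With blocks of four, only the last, incomplete block of a cell can be unequal. If 0, 1, 2 or 3 women are left over, the squared difference between arms averages 0, 1, 4/3 and 1. Assuming these remainders are equally likely, the mean is (0 + 1 + 1.33 + 1) / 4 = 0.83 per cell. One surgery type spans 7 cells, so the SD of its arm difference is √(7 × 0.83) = 2.4 women. Simple randomisation of 212 / 4 = 53 women would give √53 = 7.3. One hospital spans 4 cells: √(4 × 0.83) = 1.8, against √(212 / 7) = 5.5. Visible dissimilarity on either factor is therefore unlikely.

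**3. Power and hazard ratio.** The article gives no return times by surgery type, so the strength of that factor is assumed and varied. *Inputs from the article:* 191 women, 28 cells, blocks of four, HR 1.5, censoring at 26 weeks. *Assumptions:* 1.5 is the HR within surgery type; Weibull times with shape 1.5; median 8 weeks for control women in the fastest type; surgery mix 30/25/20/25% from fastest to slowest; equal-sized hospitals with no hospital effect; log hazards equally spaced across types. The span is the hazard of the fastest type divided by that of the slowest. There were 4,000 runs per row; the Monte Carlo SE is √(0.77 × 0.23 / 4000) = 0.7 points.

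| Span | Unadjusted log-rank | Log-rank stratified by surgery | Cox adjusted for surgery | Log-rank on 28 cells | HR unadjusted | HR adjusted |
|---|---|---|---|---|---|---|
| 1 | 76.7% | 74.7% | 77.0% | 64.1% | 1.50 | 1.51 |
| 1.5 | 76.6% | 75.5% | 78.4% | 65.6% | 1.49 | 1.51 |
| 2 | 74.1% | 76.5% | 78.7% | 65.9% | 1.47 | 1.52 |
| 3 | 67.2% | 75.0% | 77.1% | 65.0% | 1.43 | 1.51 |

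Comparisons belong within a row, because events fall from 189 to 176 as the slower types become slower. The first row lies below 80% for reasons unrelated to strata: a few women are censored, and the Schoenfeld formula is slightly optimistic here (Freedman's asks for 197).

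**4. Type I error** (HR 1.0; spans 1, 2 and 3). Unadjusted log-rank 5.0, 4.6 and 4.3%. Log-rank stratified by surgery 5.2, 5.3 and 5.6%. Wald test from the surgery-adjusted Cox model 5.2, 5.8 and 5.7%. The SE is √(0.05 × 0.95 / 4000) = 0.34 points.

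**5. Adding a hospital effect** (1,500 runs; Cox model with surgery type and hospital indicators). At span 2 with a between-hospital log-hazard SD of 0.15, power is 72.5% unadjusted against 77.3% adjusted. At span 3 with SD 0.2, it is 64.5% against 74.1%. Type I error of this larger model's Wald test was 5.1 to 6.6% over four scenarios (SE 0.56 points), perhaps a little liberal.

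**The case against.** **The article is condensed.** A reader might infer that the analysis ignores the strata. That is an inference from silence: a fuller plan may name them, and leaving model terms to it is normal. This stands. What the article does state is the conditional rule, and a plan that adjusted whatever the balance would contradict that sentence.

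**Surgery type may hardly matter.** The Background attributes time to return mainly to patient and employer expectations rather than to type of surgery. If so, nothing is lost by omitting it, as the first row shows, and a log-rank stratified by surgery even costs about two points. This stands, and it is why the loss is given as a range starting at zero. The same passage, however, supports prespecified adjustment for expectations, which are measured at baseline.

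**Dilution against the planned 1.5.** A reader might infer that the analysis estimates less than was planned for. The Sample size section pools all surgeries, so 1.5 may well be a pooled ratio, which an unadjusted analysis targets directly. Pooled and within-type hazard ratios are different quantities, so this reading is not established.

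**A post-randomisation covariate.** The Prognostic factors list includes "12) Complications during surgery; assessed by questions", and a reader might infer that it could enter the model. The Data analysis section speaks of dissimilarities in baseline characteristics, and this item is not one, so the documents do not support that.

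**Part of the gain is test size.** The unadjusted test runs slightly below 5% and the adjusted Wald test slightly above, so the power gap is a little flattering. It does not explain the result: at span 3 the surgery-stratified log-rank, at 5.6%, still has 75.0% power against 67.2%.

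**Blinded analysis.** Strengths and limitations says research codes keep the analysis blinded. That would reduce the risk from a late choice of covariates, but not remove the choice.

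**Conclusion.** The point holds in a limited form and should be fixed. The design stratifies on two factors, while the stated rule adjusts only for imbalance that the design itself suppresses, and it leaves the primary model open until the data are seen.

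Omitting the factors does not invalidate the test or raise the false-positive rate. The cost is power, and it cannot be fixed from the documents. For spans of 1, 1.5, 2 and 3, the gap to a surgery-adjusted Cox model is 77.0 − 76.7 = 0.3, 78.4 − 76.6 = 1.8, 78.7 − 74.1 = 4.6 and 77.1 − 67.2 = 9.9 points. The fall in the unadjusted HR from 1.50 to 1.43 applies only if 1.5 is the within-type ratio. All of this rests on the Weibull shape, medians, surgery mix and spans assumed above. If surgery type and hospital do not predict return to work, only the data-dependence of the model remains.

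**What to change.** Replace the conditional sentence in Data analysis with a rule fixed before the data are seen, for example:

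> The primary analysis is a Cox model with treatment group, type of surgery as used at randomisation (four levels), hospital (covariate or shared frailty), baseline return-to-work expectation and sick leave in the three months before baseline. It is fitted whatever the observed balance. Unadjusted Kaplan-Meier curves and the log-rank test are supportive.

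- The two named predictors are examples. What matters is that the list is short, baseline-only and fixed.
- Do not stratify the test on all 28 cells. At about 7.6 women each, that gave 64 to 66% power, below the unadjusted test at every span in the table.
- With hospital as six indicators, check the size of the Wald test. A frailty term uses fewer parameters.
- State in Sample size whether 1.5 is a pooled or a within-type hazard ratio.

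The cost is wording. Every variable is already collected, and randomisation follows completion of the baseline questionnaire. If surgery type has no effect, adjusting for it costs essentially nothing (77.0% against 76.7%). The one change in meaning is that the reported hazard ratio becomes conditional on these covariates, which the supportive unadjusted results offset.

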## Background

### Health care problem

Research on duration of full recovery and Return To Work (RTW) after (laparoscopic) gynaecological surgery has shown large discrepancy between expected physical recovery and actual return to work [1-3]. This may be explained by the fact that duration of recovery and RTW is mainly influenced by the expectations of the patient and employer, rather than by physical factors or the type of surgery [4-6]. However, in most cases there is hardly attention for RTW expectations [7]. In general, gynaecologists do discuss the needs and risks concerning the surgical intervention and expected duration of hospitalization with their patient, but structural convalescence recommendations regarding the resumption of (work) activities are mostly not provided [1,8]. In addition, after discharge the patient usually has only one post-operative check-up six weeks after surgery, which is focused on examination of the physical condition. Other medical care is fragmented and given only on demand, as a result of which patients often do not know whom to contact for support in case of postoperative complaints. Due to Dutch legislation, patients with paid work who do not RTW within six weeks after surgery, are generally consulted by their Occupational Physician (OP). However, as a result of the lack of recognised guidelines on the resumption of (work) activities and poor communication between the gynaecologists, General Practitioners (GPs) and OPs, often indistinct and conflicting recommendations are given and additionally most physicians do not differentiate according to the type of surgery [9-11]. These factors contribute to uncertainties and irrational beliefs of patients, which may result in delayed recovery, prolonged sick leave and reduced quality of life [12,13].

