### Study population

Eligible patients for this study are women aged between 18-65 years, employed for at least 8 hours per week (paid or unpaid) and scheduled in one of the participating hospitals for a laparoscopic adnexal surgery and/or hysterectomy due to benign disorders. Exclusion criteria for this study are: 1) (suspicion of) malignancy; 2) (ectopic) pregnancy; 3) deep infiltrating endometriosis; 4) concomitant surgical procedures or major health problems/psychiatric disorders affecting recovery or daily activities; 5) being sick listed for more than 4 weeks, or when the surgery is to cure the reason of the absence of work, sick listed for more than 2 months; 6) working temporarily for an employment agency without detachment; 8) dealing with a lawsuit against their employer; 9) not able to understand or complete the questionnaires written in the Dutch language and 10) no access to internet.

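### The primary return-to-work analysis is adjusted for baseline prognostic variables only if the arms look dissimilar, which forgoes power and leaves covariate choice open until the arms have been compared

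*Protocol article*

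**What the plan says.** Under Data analysis, the Protocol article first compares baseline characteristics between the arms descriptively, then adjusts for prognostic differences where that is judged necessary. It gives no threshold and no list of variables. The primary outcome is described with Kaplan-Meier curves and a log-rank test by allocated group, and "The Cox proportional hazard model will be used to estimate hazard ratios for RTW and the corresponding 95% confidence interval".

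Under Prognostic factors, item 15 is "Sick leave duration in the past 3 months" and item 16 is "Expectations, intention and motivation of the employee about return to work after surgery". Table 3 places both at baseline, and the Randomization section allocates a woman only after her baseline measurements are complete.

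On why return to work is slow, the Health care problem section offers a possible explanation: "duration of recovery and RTW is mainly influenced by the expectations of the patient and employer, rather than by physical factors or the type of" (the last item being the type of operation). The Discussion also calls beliefs about recovery and return to work prognostic.

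The Sample size section reads "To achieve a power (1-β) of 80%, with a significance level (α) of 5" per cent, "considering a HR of 1.5 in favour of the intervention group", and arrives at about 191 patients, raised to at least 212 for 10% drop-out.

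**The concern.** Observed imbalance is a poor reason to adjust or not to adjust. In a Cox model a covariate that predicts the outcome sharpens the treatment comparison even when the arms are perfectly balanced on it. A rule tied to dissimilarity therefore drops the covariate in just the datasets where it would still have helped.

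The rule also leaves the content of the primary model undecided until somebody has looked at the arms. The Blinding section says that researchers cannot be blinded to allocation. The Strengths and limitations section says that coded data allow a blinded analysis, which lessens the worry, but no pre-stated criterion limits the choice.

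At stake is power that costs no extra patient, in a trial whose size follows exactly from its effect assumption, and a primary hazard ratio whose definition (adjusted or not, and for what) is not fixed in advance.

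**Working it through.** **1. The plan's own figure.** Inputs from Sample size: power 80%, alpha 5% (sidedness not stated; two-sided reproduces the figure), hazard ratio 1.5. Allocation is about 1:1 (Randomization). Schoenfeld's formula without covariates:

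events = 4(1.96 + 0.84)² / (ln 1.5)² = 190.97, so 191.

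This matches the stated number. For drop-out, 191 / 0.9 = 212.2, against the stated 212. The count contains no covariate, so it fits the unadjusted analysis.

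**2. What has to be assumed.** The article gives no strength of association between items 15 and 16 and time to return to work. Let x be a standard normal combined baseline score with correlation rho with log time. With exponential times and hazard exp(b·arm + g·x),

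rho² = g² / (g² + π²/6), so g = 1.283·rho / √(1 − rho²).

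This gives g = 0.40, 0.56 and 0.74 at rho = 0.3, 0.4 and 0.5.

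**3. Power with and without x.** Simulated Cox Wald tests, two-sided 5%, 191 women, all with events (what the plan's count implies). The coefficient b was set so that the *unadjusted* hazard ratio is about 1.5. Each row has 3,000 or 4,000 runs; the Monte Carlo standard error at 80% and 3,000 runs is √(0.8 × 0.2 / 3000) = 0.7 points.

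| rho | Unadjusted power | Adjusted power | Gain (points) |
|---|---|---|---|
| 0.15 | 77% | 80% | 3 |
| 0.2 | 77% | 81% | 4 |
| 0.3 | 78% | 86% | 8 |
| 0.4 | 77% | 90% | 13 |
| 0.5 | 77% | 95% | 18 |

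At rho = 0.1 a run was made only with 1.5 as the conditional hazard ratio: 77% v 78%, a gain of 1 point. With 10% of women censored, the results at 0.3, 0.4 and 0.5 are 75% v 83%, 77% v 89% and 77% v 95%.

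**4. A second, independent simulation** (2,500 runs, strength set as hazard ratio per SD of the score, unadjusted hazard ratio again about 1.5) gave:

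- 1.35 per SD (rho about 0.23): 80% v 84%
- 1.65 per SD (rho about 0.36): 79% v 91%
- 2.0 per SD (rho about 0.48): 81% v 97%

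**5. A rougher approximation.** Power = Φ(2.80 / √(1 − rho²) − 1.96) gives 84%, 86% and 90% at rho = 0.3, 0.4 and 0.5, so gains of 4, 6 and 10 points. It is lower because it ignores that the covariate-conditional hazard ratio exceeds the marginal one (1.56, 1.63 and 1.72 in step 3).

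**6. Does adjustment do harm?** With no prognostic effect, power is 79.6% unadjusted and 79.4% adjusted. Under the null, type I error is 4.8% and 5.5% unadjusted, and 5.6% and 5.2% adjusted, for two strengths of covariate. The standard error is √(0.05 × 0.95 / 2500) = 0.4 points, so all are compatible with 5%.

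**The case against.** The strongest reply is that nothing here is invalid: the unadjusted test holds its level, and this is a condensed article whose covariate list may sit in an analysis plan that is not shown. Both points are fair. A missing list would be no finding. What the article does state is the trigger, and that is what needs changing.

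Four stronger readings are tempting, and the documents do not support them.

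- *The trial misses its 80%.* If 1.5 were the covariate-conditional hazard ratio, unadjusted power would be 68%, 62% and 53% at rho 0.3, 0.4 and 0.5, against about 78% adjusted. The article never says that 1.5 is conditional, and 191 is the covariate-free count. On the natural marginal reading, power stays near 80%.
- *The hazard ratio is biased towards 1.* The unadjusted hazard ratio is smaller than the conditional one because hazard ratios are not collapsible. It remains a valid marginal estimate.
- *Expectations are established as the main driver, and the randomisation factors as weaker.* The Background wording is hedged and includes the employer's expectations, while item 16 covers only the employee's. It ranks expectations above physical factors and type of surgery, but says nothing about hospital or prior sick leave. The section on usual care says that counselling differs between hospitals.
- *Prior sick leave is bound to vary widely.* Study population excludes women "being sick listed for more than 4 weeks, or when the surgery is to cure the reason of the absence of work, sick listed for" (the second limit is two months). That caps the range, so item 15 may be only moderately informative.

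It also stands that the size of the gain is assumed, and that it is small if the covariates are weak.

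**Conclusion.** The point holds as a recommendation to improve a stated rule. Tying adjustment to observed dissimilarity is the wrong criterion, and it leaves the primary model open until the arms have been compared. The planned analysis is valid, but it gives up power that data already collected could supply.

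The direction does not depend on the assumed correlation, provided the covariates are prognostic, as the article lists them. The size does depend on it: about 1 to 4 points below rho 0.3, about 8 at 0.3 and up to about 18 at 0.5. The simulations also assume proportional hazards given the score, one correctly specified linear score, and events in all 191 women. The gains were similar with 10% censored from rho 0.3 upwards. The randomisation factors were not simulated.

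**What to change.** In Data analysis, replace the imbalance trigger with a pre-specified primary Cox model, fitted regardless of observed balance, that contains:

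- treatment group;
- one pre-named measure from item 16 (the item covers three constructs and no single score is described, so the choice must be made and written down);
- sick-leave duration in the past three months (item 15);
- the randomisation factors, type of surgery and hospital, as strata or as terms.

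Take the primary p-value and hazard ratio from this model. Report the Kaplan-Meier curves, log-rank test and unadjusted hazard ratio as supportive.

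The cost is wording, settled before anyone compares outcomes by arm. It needs no new data, because both items belong to the baseline measurements completed before randomisation. The model spends two degrees of freedom if each covariate enters as a single term, and more if the randomisation factors enter as indicators (six for seven hospitals, plus those for type of surgery). The adjusted hazard ratio is a conditional effect and should be labelled so beside the marginal one.
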